### Data statistical analysis

On the basis of the intention-to-treat (ITT) principle, SPSS version 22.0 (Chicago, IL, USA) will be recommended to run the data statistical analysis on both the real APP group and the sham APP group. Information on all patients in the random list should be included in the final analysis. If data is missing, the missing data imputation should be used to analyze the validity of the statistical analysis. The statistical description of categorical variables (the population demographic data) will be mainly presented by the relative number (rate, proportion, and ratio). The continuous variables (repeated measurement data of three physiological parameters) will be compared by analysis of variance (ANOVA) or the Kruskal-Wallis test (or chi-squared tests) for the two groups. Other categorical variables (data on satisfaction from caregiver, acceptance from patient, and additional use of analgesics) will be described by the nonparametric test (Wilcoxon’s rank sum test). A two-sided *P* value < 0.05 will be considered to be statistical significance. Therefore, subjects’ personal information, such as nationality, education, and medication history, will be used to consider whether to perform statistical analysis in subgroups.

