### Measurement

Each patient’s demographic data (age, sex, nationality, educational background, marital status, occupation before retirement, personal income per month, history of taking medicine, chronic case history) will be recorded by a self-designed questionnaire. Other information including physiological parameters (heart rate, blood pressure, and oxygen saturation), sore spot, pain score, adverse effects, the use of analgesics in the intervention, satisfaction of caregivers, and acceptance of patients, will be more rigorously documented. The MoCA is made to identify the severity of dementia among the patient. And locality of the pain will be shown clearly according to the Brief Pain Inventory Chinese version (BPI-C) [25]. The FPS-R with great reliability and validity will be elected to assess pain intensity, and three physiological parameters are monitored with electronic sphygmomanometer (OMRON, HEM-7120) and Fingertip Oximeter (PC-60B). The data required for the study include pain score, noninvasive monitoring of blood pressure, heart rate collected at baseline (before performing the intervention, T0), at 5 min during performing the intervention (T1), and at 5 min after the intervention finished (T2) as well as digital monitoring of oxygen saturation. The intervention process of APP should be closely monitored, even if there are no reports of its side effects. And it will be recorded in detail and properly handled for any adverse reactions observed. The use of analgesics in the intervention also will be carefully recorded to enhance analysis of the safety and analgesic effect of APP. Satisfaction from caregivers will be surveyed via a 5-point satisfaction scale (5, very satisfied; 4, satisfied; 3, uncertain; 2, dissatisfied; 1, very dissatisfied) at T2 [26]. However, acceptance of patients will be measured by just asking them if they would like to accept the APP treatment once again.

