### Outcome measurement

#### Primary outcome measure

The level of pain relief at T1 and T2 will be considered as the primary outcome. It is accurately recorded by a researcher in charge of recording on the basis of the FPS-R.

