### Sample size estimation

After obtaining the ethical approval of our study protocol, a preliminary experiment with a sample size of 30 was conducted in Nursing Home, Yinchuan, in January 2020. The results of the pilot study indicated that the FPS-R score of the control group and the intervention group was 5.97 ± 1.81 and 4.79 ± 1.96, respectively. We have consulted a statistician from the School of Medical Statistics and Epidemiology at Ningxia Medical University, who finished the randomization list of the recruits. With a type 1 error rate of 0.05 (*α* = 0.05, two-tail) and a 90% power (*β* = 0.10), the sample size of the study scheme was calculated by the statistical expert, which was 86 patients in each group. According to our study design and considering the particularity of this research subject (they are less likely to complete the entire experiment), we assume a 20% drop-out rate. The total sample size of 206 cases (per group was 103 cases) is required to reduce the underpower of the study.

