## Abbreviations

APP: Auricular point acupressure
ANCOVA: Analysis of covariant
BPI-C: Brief Pain Inventory Chinese Version
CONSORT: Consolidated Standards of Reporting Trials
DMSMC: Data Management and Safety Monitoring Committee
DMS-VI: Diagnostic and Statistical Manual of Mental Disorders-VI
FPS-R: Face Pain Scale Revised
ITT: Intention-to-treat
MoCA: Montreal Cognitive Assessment
NSAIDs: Non-steroidal anti-inflammatory drugs
SAF: Supervised compliance form
TCM: Traditional Chinese medicine

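### The analysis section names no test for the primary outcome, leaves pain relief undefined, and does not use the T0 pain score as a covariate

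*Protocol article*

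**What the plan says.** Under Primary outcome measure, the protocol states: "The level of pain relief at T1 and T2 will be considered as the primary outcome". The next sentence ties it to the scale: "It is accurately recorded by a researcher in charge of recording on the basis of the FPS-R". Table 1 schedules the FPS-R at enrolment, T0, T1 and T2, and the Measurement section confirms the baseline reading: "The data required for the study include pain score, noninvasive monitoring of blood pressure, heart rate collected at baseline", followed by T1 and T2.

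Data statistical analysis then goes through the variables:

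- Demographic data are described by rates, proportions and ratios.
- For continuous data: "The continuous variables (repeated measurement data of three physiological parameters) will be compared by analysis of variance (ANOVA) or the Kruskal-Wallis test", with chi-squared tests as a further option.
- For several other outcomes: "Other categorical variables (data on satisfaction from caregiver, acceptance from patient, and additional use of analgesics) will be described by the nonparametric test", namely Wilcoxon's rank sum test.

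The FPS-R, the pain score and pain relief are not mentioned in that section. The Abbreviations list contains "ANCOVA: Analysis of covariant", but the term is used nowhere in the text.

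**The concern.** The section does not simply defer its tests to a later document. It settles them for named secondary outcomes and passes over the outcome on which the trial is sized.

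Two things are left open as a result. One is the quantity: pain relief could be the FPS-R score at T1 or T2, the change from T0, or a percentage change. The sample size section works with group FPS-R scores, while the word relief points towards change. The other is the test. With both open, the primary result could be chosen after the data are seen.

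The continuous methods that are stated, even if carried over to the FPS-R, do not adjust for T0 pain as a covariate. A comparison of scores at T1 or T2 alone leaves any chance T0 imbalance in the estimate and forgoes precision that data already collected would provide.

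**Working it through.** **1. Outcomes against methods.**

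| Outcome | Test named in Data statistical analysis |
|---|---|
| FPS-R pain relief at T1 and T2 (primary) | none |
| Blood pressure, heart rate, oxygen saturation | ANOVA or Kruskal-Wallis (or chi-squared) |
| Satisfaction, acceptance, additional analgesics | Wilcoxon rank sum |
| Adverse reactions, duration of intervention | none |

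**2. Inputs.** From Sample size estimation: pilot FPS-R 5.97 (SD 1.81) in control and 4.79 (SD 1.96) in intervention; two-sided alpha 0.05; power 90%; 86 per group; 20% drop-out; 103 per group randomised. Derived:

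- difference 5.97 − 4.79 = 1.18
- pooled SD √[(1.81² + 1.96²)/2] = 1.886
- d = 1.18/1.886 = 0.63
- evaluable per arm 103 × 0.8 = 82.4, taken as 82

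The correlation r between T0 and later FPS-R is not in the protocol; 0.3, 0.5 and 0.7 are assumed.

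**3. The plan's own figure.** n per group = 2(1.960 + 1.282)² × 1.886²/1.18² = 53.7, so 54 (55 with the t distribution). The stated 86 does not follow from the stated inputs. That is a separate matter; here it shows only that the stated size exceeds what the pilot effect requires.

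**4. Unadjusted comparison.** SE = 1.886 × √(2/82) = 0.295. Power at the pilot difference = Φ(1.18/0.295 − 1.96) = Φ(2.04), about 98%.

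**5. Baseline-adjusted comparison.** ANCOVA multiplies the variance by 1 − r², so SE = 0.295 × √(1 − r²). The equivalent gain in patients is 1/(1 − r²) − 1, and the 95% interval half-width is 1.96 × SE.

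| Assumed r | Variance cut | SE | Half-width | Equivalent extra patients |
|---|---|---|---|---|
| unadjusted | – | 0.295 | 0.58 | – |
| 0.3 | 9% | 0.281 | 0.55 | 10% |
| 0.5 | 25% | 0.255 | 0.50 | 33% |
| 0.7 | 49% | 0.210 | 0.41 | 96% |

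**6. Effect on power.** At the pilot difference, power moves from about 98% to Φ(1.18/0.281 − 1.96) = 98.7% at r = 0.3 and Φ(1.18/0.255 − 1.96) = 99.6% at r = 0.5. There is little left to gain.

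**The case against.** **The protocol may leave this to an analysis plan.** A separate plan may exist, and the unused ANCOVA abbreviation may hint that baseline adjustment was intended. This is fair as far as it goes, but an abbreviation assigns no method to any outcome. Nor is the section silent on tests: it fixes them for named secondary outcomes and omits the primary.

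**An unadjusted randomised comparison is valid.** True. The case for adjustment is efficiency, and its size depends on a correlation that the protocol does not report. That limits the claim to precision; it does not remove it, since adjustment costs nothing and the variance cut is r² whatever r is.

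Some stronger readings are tempting but not supported:

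- *Only the primary outcome lacks a test.* Adverse reactions and duration of intervention, both listed as secondary, lack one too.
- *The stated methods discard T0 altogether.* The continuous methods are described for repeated measurements, so a repeated-measures ANOVA with T0 as one time level is a possible reading. The text does not extend it to the FPS-R, and it would not be covariate adjustment.
- *The trial is underpowered without adjustment.* On its own pilot figures it is not.
- *A change score would be less precise than the raw score.* With k the ratio of the T0 SD to the later SD, that holds only when r is below k/2. The protocol gives neither quantity, and entry at FPS-R ≥ 4 could make k less than 1.
- *Nursing home must be in the model.* The article describes no stratification by site, so this is optional.

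**Conclusion.** The point holds in limited form. The protocol names no analysis for its primary outcome, does not define pain relief as a raw score or a change, and states no method that adjusts for baseline pain as a covariate, although T0 FPS-R is collected. These are textual facts and rest on no assumption.

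The benefit of correcting this is a fixed primary estimate and a narrower interval: a variance reduction of 9% to 49% for assumed correlations of 0.3 to 0.7. The SE figures further assume the pilot SD of 1.886, 82 evaluable patients per arm, and a linear relation between T0 and later scores that is similar in both arms. The point should be settled but does not threaten the trial's validity or its power.

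**What to change.** Add a primary-analysis statement to Data statistical analysis:

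- Analyse post-intervention FPS-R by ANCOVA with arm and T0 FPS-R as terms. Alternatively, because the primary outcome covers both T1 and T2, use a mixed model over the two times with T0 FPS-R, arm, time and arm-by-time. Say which time, or which combination of the two, the primary estimate refers to.
- Define pain relief as the baseline-adjusted between-group difference in FPS-R, and report it with a 95% confidence interval.
- Optional: a rank-based sensitivity analysis, since a faces scale is ordinal, and nursing home as a covariate.

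The cost is wording only. T0 FPS-R is already in the assessment schedule, the nursing home of each patient is known, and the named software can fit the model. The statement should be fixed before unblinding.

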## Methods

### Study design

This study is a multi-center and single-blind, randomized, sham-controlled clinical trial. It aims to compare and analyze the one-time analgesic effect between the intervention group and the sham-controlled group (Fig. 1, Table 1) for acute pain in patients with dementia. This trial, superiority framework, was designed on the basis of SPIRIT guidelines and the Consolidated Standards of Reporting Trials (CONSORT) statement [18, 19]. The Ningxia Medical University Ethics Committee has given its official approval for the study protocol, which has been registered at the Chinese Clinical Trial Registry (No.: ChiCTR2100047932). Each patient will be given a detailed explanation by the researcher including the purpose, benefits, and potential risks of the study. Moreover, they can withdraw from the study at any time, and this will not affect medical services other than the research. Subsequently, the qualified recruits who signed informed consent entering the study will receive APP or shamed APP treatment by an investigator, a master candidate in nursing science with APP professional training. It is needed to make important protocol modifications to reduce underpower of the study protocol and increase patient safety. We will communicate with the Data Management and Safety Monitoring Committee (DMSMC), all participants, and the Ethics Committee.

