### Study setting

This randomized controlled trial is being conducted at three nursing homes in Yinchuan, China. These institutions are urban and public in the region, with approximately 2000 permanent residents.

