### Patients

All 206 patients who met the inclusion and exclusion criteria are being recruited from the three nursing homes. Recruitment is expected to take place from December 2020 to December 2021. The recruits with informed consent before entering research will be randomly allocated to an intervention or a sham-controlled group in a 1:1 ratio. Furthermore, it is feasible to have enough patients to meet the target sample size in three nursing homes. The inclusion criteria include the following: (1) aged 60 or above with speaking Chinese, (2) dementia was diagnosed by the Diagnostic and Statistical Manual of Mental Disorders (DMS-V) criteria [20], (3) diagnosis of mild dementia based on the Montreal Cognitive Assessment (MoCA) [21], (4) acute pain and a score of pain ≥ 4 based on the Face Pain Scale Revised (FPS-R), (5) able to be monitored by pulse oximetry, (6) understanding the meaning of the FPS-R, and (7) volunteering to participate in the study and signing the informed consent (caregivers, patients, and/or family members). The exclusion criteria are as follows: (1) moderate or severe dementia, (2) medical contraindication for ear acupressure (inflammation, ulcers, frostbite in the ear), (3) history of allergy to adhesive tape and alcohol, (4) critically ill patients who have no response to the effectiveness and safety of new treatments (serious heart, brain, liver, kidney, or hematopoietic system diseases), and (5) patients who received drugs for pain management and other interventions. Once the subjects were enrolled, written informed consent from all patients and their caregivers was obtained by the researchers.

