
### Randomization and blinding

Sequence numbers of the patients with dementia will be generated by a computer-produced random list, which is performed by a statistical expert from Ningxia Medical University. But she is independent of the trial. The randomization schedule in a sealed envelope will be kept in a dedicated research office. There are many strategies to ensure the concealment of data distribution and minimize selection bias as well as create a double-blind environment. It will be blind to the randomized lists for participants (e.g., other researchers, patients, and caregivers) except the investigator responsible for conducting the intervention [24]. The project manager can suspend blinding until all the trials have been carried out according to the rules. The research team is responsible for reducing the rate of loss of intervention. Prior to the trial, the researcher went into the nursing home and lived and worked with the caregivers of the elderly to learn about the patient’s lifestyle. Meanwhile, they obtained their and their caregivers’ support and cooperation. Patients and their caregivers will be presented face to face with detailed information, which includes intervention process, collection and use of data and biological specimens, benefits, and potential adverse reactions from the trial [23]. But patients also have the right to withdraw from the study at any time without affecting subsequent care. In case patients and (or) their caregivers decide to quit the trials, data and biological specimens will be destroyed. It has been also documented in the informed consent form.

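### Three nursing homes, but no stratification by home is described and the tests named for the secondary outcomes carry no home term: a modest, avoidable loss of precision

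*Protocol article*

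**What the plan says.** Study design: "This study is a multi-center and single-blind, randomized, sham-controlled clinical trial". Study setting: "This randomized controlled trial is being conducted at three nursing homes in Yinchuan, China".

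Under Patients, recruits are "randomly allocated to an intervention or a sham-controlled group in a 1:1 ratio", so the unit of randomisation is the patient, not the home. Under Randomization and blinding, the only description of the sequence is that it "will be generated by a computer-produced random list". Neither section mentions home, strata or blocks.

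Data statistical analysis then assigns tests by outcome:
- The first assignment is limited in scope to "The continuous variables (repeated measurement data of three physiological parameters"). Of these, the section states that they "will be compared by analysis of variance (ANOVA) or the Kruskal-Wallis test (or chi-squared tests) for the two groups".
- Caregiver satisfaction, patient acceptance and additional analgesic use "will be described by the nonparametric test (Wilcoxon’s rank sum test").

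No home term appears in either assignment. The section names nationality, education and medication history as possible subgroup variables, but not home. It names no test for the FPS-R, which is the primary outcome.

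**The concern.** Home is known for every patient and is part of the design. Homes may differ in the causes of pain, in usual care and, for the satisfaction scale, in how their caregivers rate.

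Two cases are possible, and neither is served by an analysis without home:
- **List not stratified.** The arms can be spread unevenly over homes by chance. Differences between homes then enter the observed treatment difference, and between-home variation sits in the residual.
- **List stratified by home.** The arms are balanced within homes, but a test without home still counts between-home variation as error, so its standard error is too large.

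At stake is precision, and protection of the result against a chance imbalance that the analysis could have absorbed.

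**Working it through.** The plan gives no figure for between-home variation, so there is none to reproduce. Home sizes and the ICC (the share of outcome variance lying between homes) are assumptions throughout.

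**Inputs from the article.** 206 patients, 103 per group, 1:1, three homes; 86 per group before the drop-out allowance, so 2 × 86 = 172 completers; pilot SDs 1.81 and 1.96; two-sided α 0.05, power 90%. The 86 is taken as stated.

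**1. Chance imbalance without stratification.** Assume homes of 69, 69 and 68. Worse than 60:40 means a larger arm of at least 42 in a home of 69 (42/69 = 0.609) or at least 41 in a home of 68 (41/68 = 0.603).

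- *Coin-flip list.* Binomial(h, 0.5) gives 0.091, 0.091 and 0.114 for the three homes. P(at least one) = 1 − 0.909 × 0.909 × 0.886 = 0.27. For arms differing by 10 or more, the home probabilities are 0.228, 0.228 and 0.275, so P(at least one) = 1 − 0.772 × 0.772 × 0.725 = 0.57.
- *List fixed at 103:103, ignoring home.* P(a, b, c) = C(69,a) C(69,b) C(68,c) / C(206,103) with a + b + c = 103. Summing over the relevant splits gives 0.11 and 0.33.

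| Event in at least one home | Fixed 103:103 | Coin flip |
|---|---|---|
| Worse than 60:40 | 11% | 27% |
| Arms differ by 10 or more | 33% | 57% |

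**2. Worth of adjustment in patients.** Removing between-home variance scales the error variance by (1 − ICC), so the gain is about 172 × [1/(1 − ICC) − 1].

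| Assumed ICC | 1/(1 − ICC) | Gain on 172 |
|---|---|---|
| 2% | 1.020 | 3.5, about 4 |
| 5% | 1.053 | 9 |
| 10% | 1.111 | 19 |

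**3. Type I error and power for FPS-R.** Simulation with 172 completers, assumed home shares of 40%, 35% and 25%, and 6,000 runs per setting. Pooled SD = √[(1.81² + 1.96²)/2] = 1.886. The effect that 86 per arm detects with 90% power is 1.886 × √(2/86) × (1.960 + 1.282) = 0.93 points.

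- *Type I error, unstratified list, unadjusted test:* 0.049 to 0.051 over ICCs of 0 to 0.20. The mean estimate stays on target.
- *Type I error, stratified list, unadjusted test:* 0.041 at ICC 0.05, 0.047 at 0.10 and 0.036 at 0.20. These are at or below 0.05, as expected when the standard error is too large.
- *Power at 0.93 points:*

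| ICC | Unstratified, unadjusted | Unstratified, home in model | Stratified, unadjusted | Stratified, home in model |
|---|---|---|---|---|
| 0.05 | 0.900 | 0.906 | 0.903 | 0.907 |
| 0.10 | 0.908 | 0.922 | 0.924 | 0.932 |
| 0.20 | 0.914 | 0.947 | 0.932 | 0.951 |

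At the larger pilot effect (5.97 − 4.79 = 1.18) power is already about 98%. At ICC 0.10 with an unstratified list it moves from 0.982 to 0.990 when home is added.

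**The case against.** The strongest reply is that the article is silent, and silence is not a statement. Stratification details and model covariates are often left to the full protocol or analysis plan. ANCOVA appears among the abbreviations without being used in the text, which may hint at a covariate model set out elsewhere, and ANOVA can take a second factor. This stands in part. A reader might infer that the list ignores the homes, but the article says only that it was computer-produced. What remains is that the tests named for the secondary outcomes are two-group tests without home, and that home belongs in the analysis whichever way the list was made.

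Three further inferences are not supported:
- *That the primary analysis omits home.* The sentence naming ANOVA and Kruskal-Wallis covers the three physiological parameters. No FPS-R test is named, so none can be said to exclude home.
- *That the result would be biased or the error rate inflated.* Patients are randomised individually. The simulation shows no average bias, and the unadjusted test holds its level under an unstratified list.
- *That caregivers' rating habits distort the pain outcome.* Patients must understand the FPS-R to be eligible and a researcher records it. Caregivers rate only satisfaction.

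It is also fair that between-home variation may be small. The homes are urban public institutions in one city, data collectors are fixed and trained, and the response is measured within minutes. This argues for the lower end of the ICC range, where the gain is a few patients.

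**Conclusion.** The point holds as a modest loss of precision. The trial has three homes, describes no stratification by home, and names secondary-outcome tests with no home term. With three equal homes, the chance that some home is split worse than 60:40 is 11% to 27%, depending on whether an unstratified list fixes the totals. At ICCs of 2% to 10%, adjustment is worth about 4 to 19 patients on 172 completers. At the effect that 86 per arm detects, adding home to the model gains about half a power point to three points over ICCs of 0.05 to 0.20.

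Home sizes and ICCs are assumptions; the article gives neither. The trial's validity is not in question. The reason to act is that the change costs almost nothing and is right under either form of the list.

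**What to change.** Before unblinding, add to the analysis text:
- nursing home as a fixed factor in the model for FPS-R (still to be named) and in the models for the three physiological parameters;
- a van Elteren test stratified by home for caregiver satisfaction;
- Mantel-Haenszel analyses stratified by home for patient acceptance and additional analgesic use;
- a statement of whether the random list was stratified by home.

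The cost is two degrees of freedom (3 − 1) and a few lines of text; no new data are needed. With no between-home variation, the simulated power changed by less than half a point (0.895 without home, 0.892 with it, unstratified list, effect 0.93). There is no case for reissuing the list: Sample size estimation reports it as finished, and the analysis change captures most of the benefit.

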#### Secondary outcome measures

Secondary *outcome measures* will consist of physiological parameters, any adverse reactions observed, satisfaction from caregivers, acceptance of patients, and additional use of analgesics during the intervention. The duration of the intervention will also be included in the secondary outcomes.

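### The tests listed for the repeated physiological readings do not fit them: chi-squared does not apply, Kruskal-Wallis cannot link readings, and no method is said to adjust for T0 (secondary outcomes only)

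*Protocol article*

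**What the plan says.** **Physiological readings.** Under Data statistical analysis the protocol states: "The continuous variables (repeated measurement data of three physiological parameters) will be compared by analysis of variance (ANOVA"), and it gives as alternatives "the Kruskal-Wallis test (or chi-squared tests) for the two groups". Under Measurement, the readings are taken at baseline (T0), "at 5 min during performing the intervention (T1), and at 5 min after the intervention finished (T2"). Each patient therefore contributes three linked values per parameter.

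**Other secondary outcomes.** The same section continues: "Other categorical variables (data on satisfaction from caregiver, acceptance from patient, and additional use of analgesics) will be described by the nonparametric test", and names this test as Wilcoxon's rank sum. The three outcomes are on different scales:

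- Satisfaction is ordinal: "Satisfaction from caregivers will be surveyed via a 5-point satisfaction scale".
- Acceptance is a single question: "acceptance of patients will be measured by just asking them if they would like to accept the APP treatment once again".
- Analgesic use is listed under Secondary outcome measures as "additional use of analgesics during the intervention", with no scale given.

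**Criterion.** The inferential rule is a two-sided P "value < 0.05 will be considered to be statistical significance". Analysis of covariance appears in the abbreviation list, but the text assigns it to no outcome.

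**The concern.** The sentence on the physiological readings names the data correctly and then lists tests that do not suit them.

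- **Chi-squared** compares counts in categories. The readings are continuous and the article gives no cut-points.
- **Kruskal-Wallis** assumes independent observations. It can compare the two arms at one time, but it cannot take three linked readings per patient in one analysis.
- **ANOVA** is named without its form. It could mean a one-way test at each time, a repeated-measures ANOVA, or one run on all rows.
- **Baseline.** No method is described as adjusting for T0, although T0 is recorded before treatment and should predict T1 and T2.

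The analyses this wording allows differ in both error rate and precision, and the choice would be left until the data are in hand. The lesser issue is acceptance. A rank test on a yes/no answer gives a P value but no difference in proportions, which is the quantity a reader would want.

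**Working it through.** The plan gives no figure on this point to reproduce.

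**Inputs from the protocol.** Three readings per patient (Measurement); 103 patients per arm (Sample size estimation); two-sided 5% level (Data statistical analysis).

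**Assumption.** The protocol gives no within-patient correlation ρ, so a range of 0.3 to 0.9 is shown, with equal variances and the same ρ between every pair of times.

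**Step 1: type I error if the readings are pooled as independent rows.** With k readings per patient, the true variance of the arm difference is 1 + (k − 1)ρ times the variance assumed. The real error of a nominal 5% test is 2 × [1 − Φ(1.96 / √(1 + (k − 1)ρ))]. For k = 3 and ρ = 0.5, the factor is 2, 1.96/√2 = 1.386, and the error is 16.6%.

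| ρ | T0, T1, T2 pooled | T1, T2 pooled |
|---|---|---|
| 0.3 | 12.1% | 8.6% |
| 0.5 | 16.6% | 11.0% |
| 0.7 | 20.6% | 13.3% |
| 0.9 | 24.2% | 15.5% |

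Simulation (10,000 runs per setting, 103 per arm) agrees: 11.7%, 16.2%, 20.8% and 23.9% for three readings.

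**Step 2: type I error under the other readings of the text.** In the same simulations, the between-group test of a repeated-measures ANOVA gave 4.7% to 5.3%. Separate tests gave about 5% at each time. The chance of at least one significant result was 7% to 10% over two times and 8% to 13% over three.

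**Step 3: what the baseline is worth.** Take an effect that is equal at T1 and T2 and absent at T0. Variances of the estimated effect are in units of 2σ²/n, for n per arm:

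- Mean of T1 and T2, unadjusted: (1 + ρ)/2.
- Mean of T1 and T2, adjusted for T0: (1 + ρ)/2 − ρ².
- Group effect of an ANOVA over all three times: (1 + 2ρ)/3 × (3/2)². The factor (3/2)² arises because including T0 shrinks the expected difference to two thirds.
- Change from T0, which an arm-by-time contrast would use: (1 + ρ)/2 + 1 − 2ρ = 1.5(1 − ρ).

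| ρ | Adjusted for T0 | Unadjusted T1, T2 | Three-time group effect | Change from T0 |
|---|---|---|---|---|
| 0.5 | 0.75 − 0.25 = 0.50 | 0.75 | 0.667 × 2.25 = 1.5 | 0.75 |
| 0.7 | 0.85 − 0.49 = 0.36 | 0.85 | 0.80 × 2.25 = 1.8 | 0.45 |

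Against the unadjusted comparison, adjustment multiplies the standard error by √(0.50/0.75) = 0.82 at ρ = 0.5 and by √(0.36/0.85) = 0.65 at ρ = 0.7.

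**Step 4: yes/no outcomes.** On a 2×2 table the tie-corrected Wilcoxon statistic, squared, equals Pearson's chi-squared × (N − 1)/N. For an illustrative 20/103 against 32/103:

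- χ² = 206 × (20×71 − 32×83)² / (103 × 103 × 52 × 154) = 3.704, P = 0.0543.
- Wilcoxon: 3.704 × 205/206 = 3.686, P = 0.0549.
- The risk difference is 12/103 = 11.7 points. Its standard error is √(0.311×0.689/103 + 0.194×0.806/103) = 0.060, so the 95% CI is −0.1 to 23.4 points. The rank test does not supply this.

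Exact enumeration at 103 per arm gives a Wilcoxon type I error of 0.2%, 1.4%, 4.1%, 4.5%, 4.4% and 5.2% at true rates of 0.5%, 1%, 2%, 3%, 5% and 10%. At 30%, 50% and 80% it is 5.1%, 4.5% and 4.9%.

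**The case against.** **The figures of 12% to 24% describe an analysis the protocol does not state.** This stands. The readings are called repeated measurements just before ANOVA is named, so repeated-measures ANOVA is a natural reading, and its between-group test holds 5%. Kruskal-Wallis for two arms at one time is also valid. A reader might infer that the plan itself inflates the error rate. The text does not support that, and the figures show only what follows if the rows are pooled. An arm-by-time test in a repeated-measures ANOVA would also draw on T0 as change from baseline. By Step 3 this is still less precise than adjustment, at 0.75 and 0.45 against 0.50 and 0.36.

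**Wilcoxon on yes/no data does not give wrong error rates.** This also stands. A reader might point to a sparse table such as 0/103 against 4/103, where Wilcoxon gives P = 0.044 and Fisher's exact test 0.121. With rare events the Wilcoxon test stays below 5%, so the gap reflects Fisher's conservatism. Requiring Fisher's test would be a trade-off and would not repair a fault.

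**Effect measures may sit in a fuller document.** Accepted. A journal article commonly leaves confidence intervals and covariance structure to the full protocol or SAP, so their absence is not part of this finding.

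**The scale of analgesic use is not stated.** Accepted. If it is a dose or a count, Wilcoxon is suitable. Nor does the protocol give any rate of use.

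Two defects remain in what is written: chi-squared is attached to continuous readings, and a rank test for independent samples is offered as an alternative for repeated data.

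**Conclusion.** The point holds as a fault in how tests are matched to data for secondary outcomes. Chi-squared is wrong for the physiological readings as written, Kruskal-Wallis cannot analyse the linked readings together, and no method is said to adjust for T0.

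The effect on error depends on how the sentence is carried out. It is about 5% per test with repeated-measures ANOVA or separate tests, and about 12% to 24% only if all three readings are pooled as independent rows. The clearer cost is precision. For assumed correlations of 0.5 to 0.7, adjusting for T0 cuts the variance from 0.75–0.85 to 0.50–0.36. All these sizes rest on assumed equal variances and equal correlations, because the protocol reports none.

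For acceptance, and for analgesic use if it is recorded as yes/no, the gain is in interpretation and error control is unchanged. Wilcoxon is right for satisfaction. The primary pain outcome is not touched by this point.

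**What to change.** 1. For heart rate, blood pressure and oxygen saturation, delete the chi-squared option. Analyse T1 and T2 of each parameter with a mixed model that includes the T0 value, arm, time and arm-by-time, and allows for correlation within patients. ANCOVA at T1 and T2 adjusted for T0 is a simpler alternative.
2. For acceptance, compare proportions with a chi-squared test and report the risk difference with its 95% CI. State the scale of analgesic use, and treat it the same way if it is yes/no.
3. Keep Wilcoxon's rank sum test for the 5-point satisfaction score.

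The cost is a change of wording and slightly more programming. No new data, visits or patients are needed.
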